**Figure 2. Consent processes for England, Wales and Northern Ireland**

[figure not shown]

### Scotland

Patients will be assessed for capacity. Patients with capacity will be provided with verbal information about the trial and given a copy of the written participant information sheet. They will be given adequate time to review the information and ask questions. Due to ongoing concerns regarding risk of infection transmission, verbal consent only will be sought and documented on a study form and in the patient hospital records. Where a patient declines participation at this point they will not be entered into the study.

For patients that lack capacity, it is not practical or appropriate to consult a guardian/welfare attorney prior to enrolment without placing the potential participant at risk of harm from delaying treatment. These processes will also not be feasible or safe to undertake in order to minimise risk of viral transmission to those involved. Significant limitations have been placed on the visitation of COVID-19 patients and therefore a guardian is unlikely to be immediately be available, and to attempt contact via telephone will delay treatment. Therefore these patients will not be entered into the study, see figure 3.

**Figure 3. Consent processes for Scotland**

[figure not shown]

### **2.8.1 Consent following initial enrolment (for England, Wales and Northern Ireland only)**

Following enrolment, the participant will be followed up regularly by the hospital research team. In participants that regain capacity, the site research team will approach the participant and provide verbal information about the trial. They will also be provided with the written participant information sheet, and given adequate time to review the information sheet and ask questions. Due to ongoing concerns regarding risk of infection transmission, verbal consent only will be sought and documented on a study form and in the patient hospital records.

In participants that do not regain capacity by hospital discharge, an approach will be made to a personal consultee or professional consultee. The initial approach should ideally be made to a personal consultee. However, this will likely be precluded due to visiting restrictions, in which case the opinion of a professional consultee will be sought. The professional consultee will be a registered medical practitioner that is independent of the trial. The consultee will be provided with a verbal explanation of the trial and a copy of the written participant information sheet and cover note. If the consultee does not know of any objection to research participation expressed by the participant, they will be asked to verbally confirm this. This will be recorded on a study record form. Procedures for consent following enrolment are different in the three jurisdictions (England & Wales, Scotland, Northern Ireland). Consent processes in Northern Ireland will follow the Exception for Urgent treatment in Part 8 of the Mental Capacity Act (Northern Ireland) 2016. For this trial, the consent processes used in England & Wales will be used in Northern Ireland, with the exception that Nominated Person assent will be taken and no Nominated Consultees will be appointed. These procedures will be updated in line with updated legislation.

Under the emergency regulations that have been introduced for COVID-19 related research, in the event that the participant dies prior to regaining capacity and before consent or consultee agreement can be sought, patient identifiable information may be retained by the WCTU to complete trial analysis as per the protocol and statistical analysis plan, for sites in England, Wales and Scotland. Patient identifiable information will not be transferred or retained by the WCTU for participants in Northern Ireland that do not provide consent.

On occasion, participant consent or personal/professional consultee agreement may not be obtained prior to hospital transfer or discharge. In this circumstance, the site research team will attempt to contact the participant or their consultee (if it is known that the participant lacks mental

capacity) at their place of residence to seek agreement. Up to three attempts to contact the participant will be made. Given the urgent need to answer this research question, for sites in England, Wales and Scotland, minimal personal identifiable data (NHS or CHI number, date of birth, postcode) will be submitted contemporaneously to Warwick Clinical Trials Unit. Patient identifiable information will not be transferred or retained by the WCTU for participants in Northern Ireland that do not provide consent. In the event that a trial participant declines consent to continue in the trial, personal identifiable data will be deleted. Information collected about the participant up to the point of withdrawal will be retained for analysis.

## **2.9 Randomisation**

### **2.9.1 Randomisation**

In this trial, there may well be the possibility that the devices will not be available as a result of the challenging environment the clinical staff are presented with. For this reason, we will set up two randomisation systems, which will be integrated to maintain balance.

Prior to randomisation, the clinician/nurse will check the availability of the devices. If no device is available then there will be no randomisation. If one of the devices is available (either CPAP or HFNO), then the clinician/nurse will choose the randomisation procedure which allocates standard care and CPAP or HFNO (system 1). If both devices are available, then system 2 will allow for an allocation using the three arms (standard care, CPAP or HFNO). These two systems will be integrated and constantly updated to ensure that the allocation ratio (1:1:1 for standard care: CPAP: HFNO) is maintained if possible. There is a possibility that this ratio will not be maintained and this has been compensated for in our sample size, which has been inflated accordingly.

A simple and secure, interactive voice response (IVR) randomisation system has been established by the programming team at Warwick Clinical Trials Unit. A computer-generated randomisation sequence has been generated by the minimisation method. Patients will be stratified by site, gender (M/F), and age (<50, >=50 years). If a patient has been randomised and found to be ineligible or the device is not available, they will be included in the analysis on an intention-to-treat basis. Any data already collected will be retained and included in the analysis unless otherwise indicated.

A back-up emergency randomisation system is currently being developed and full details will be made available and maintained on the trial website.

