### **2.5.2 Exclusion criteria**

1. Planned intubation and mechanical ventilation imminent within 1 hour
2. Known or clinically apparent pregnancy
3. Any absolute contraindication to CPAP or HFNO
4. Decision not to intubate due to ceiling of treatment or withdrawal of treatment anticipated
5. Equipment for both CPAP and HFNO not available

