In our sample size calculation, we have assessed both outcome measures and taken the largest in terms of the incidence, to ensure we have maximum power and sample size for our study. Therefore taking the data from Baud *et al* to be representative of usual care and assuming a conservative incidence of 15% for the composite outcome of intubation or mortality on the usual care arm, then using a two-sided 5% significance level, a total 3000 patients (1000 per arm across 3 arms) would give approximately 90% power to detect an odds ratio of 0.625, corresponding to a reduction from 15% to 10% in the composite event rate. allowing for the 11 interim analyses. Our comparisons will be based on CPAP versus standard care and HFNO versus standard care and allow for the formal interim analyses as agreed with the DMC.

However, there remain many uncertainties regards the sample size parameters and also whether an equal randomisation allocation ratio will be maintained. For this reason we have inflated our sample size to 4000 patients (4002 across the three arms) to maintain the study power and detect small effect sizes, if they exist. It may allow us to also assess the difference between CPAP and HFNO, if difference between these interventions are small enough to be detected with this larger sample size. Furthermore, it may be likely that we will not need all these patients if the trial stops at a formal interim analysis or if the DMC recommends that an arm is dropped.

The formal stopping rules will be set out in the statistical analysis plan, following discussions with the DMC. These criteria will be used to accept or drop an intervention arm, based on the assessment of the primary outcome at each interim point.

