## **6.2 Statistical analysis of efficacy and harms**

### **6.2.4 Statistics and data analysis**

The statistical analysis will be based on intention to treat and will be conducted in line with the CONSORT statement. For the overall analyses, numbers of events will be assessed using the logistic regression unadjusted and adjusted for important predictors, such as previous morbidities, age and gender) and results will be presented using odds ratios (with 95% confidence intervals). At the interim stages, the numbers of events will be analysed using the latter methods and compared

to the p-value critical values. A final p-value and treatment effect estimate will be calculated adjusting for the interim analyses using the methods described by Jennison and Turnbull, Fairbanks and Madsen and, Emmerson and Fleming. Intubation rates and mortality at 30 days will be assessed using the logistic regression models (both for adjusted and unadjusted analyses) and summarised using odds ratio (with 95% confidence intervals). Continuous secondary data will be presented using summary statistics and analysed using parametric or non-parametric methods depending on the distribution of the data.

If possible, we will conduct a compliers average cause effect (CACE) analysis to assess the effect on the non-compliance to the allocation interventions (for all three interventions or two, if one is dropped).

We anticipate no or very little missing data. However, in the case of missingness, we will use multiple imputation techniques (ICE procedures) to assess the missingness mechanisms.

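### Two randomisation systems, chosen by device availability and steered together to 1:1:1, can let availability confound each device's comparison with standard care; the protocol's only stated remedy is a larger sample.

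*Protocol*

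**What the plan says.** Section 2.9.1 of the protocol has staff check device availability before randomisation. With one device, the patient enters system 1, which allocates standard care or that device. With both, the patient enters system 2, which allocates all three arms. With neither, there is no randomisation. On the link between the systems: "These two systems will be integrated and constantly updated to ensure that the allocation ratio" of 1:1:1 is kept if possible. If the ratio is lost, "this has been compensated for in our sample size, which has been inflated accordingly". Minimisation is on site, gender and age group; availability is not a factor.

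Section 6.1 defines the contrasts: "Our comparisons will be based on CPAP versus standard care and HFNO versus standard care". Section 6.2.4 analyses by intention to treat, with event numbers "assessed using the logistic regression unadjusted and adjusted for important predictors, such as previous morbidities, age and gender", and uses the same methods at the interims. Section 6.1 says that the primary outcome at each interim will be used to accept or drop an arm. Neither section says which standard-care patients serve as controls for which device.

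Section 2.5.2 lists as exclusion 5: "Equipment for both CPAP and HFNO not available".

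**The concern.** A standard-care patient entered when only CPAP was available had no chance of HFNO. If that patient counts as an HFNO control, that part of the contrast is not randomised. Steering to an overall 1:1:1 adds a second problem: the ratio of device to standard care then differs between one-device and two-device settings, so even patients who were randomised against each other are not balanced unless the analysis stratifies.

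Either route produces bias only where patients in better- and worse-equipped settings differ in risk. That is plausible: sections 1.4 and 2.9.1 describe equipment shortage and a difficult working environment, which may vary by site and over time. A spurious benefit or harm could then appear, and an interim decision on an arm could rest on it. Extra patients would narrow the interval around the wrong value and raise the false rejection rate.

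**Working it through.** **The plan's own figure.** Section 6.1 claims about 90% power for 15% v 10% with 1000 per arm at two-sided 5%, allowing for 11 interims. A fixed two-proportion test gives 92.3%. An O'Brien-Fleming boundary with 12 equally spaced looks, by simulation, gives 91.3%. The claim is reproduced. With 1334 per arm the fixed-design power is 97.4%. All of these assume that every standard-care patient is a valid control.

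**Inputs for the bias check.** From the protocol: N = 4002, so 1334 per arm at 1:1:1, and two-sided 5%. Assumed, because the protocol gives nothing: a share f of patients enters when only CPAP is available, the rest enter when both devices are, and there is no treatment effect. Let r1 and r2 be the risks in systems 1 and 2.

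**Allocation at f = 0.3.** System 1 has 4002 × 0.3 ≈ 1200 patients. HFNO's 1334 patients all come from system 2. Two schemes both hold 1:1:1 overall:
- A, system 1 at 1:1: 600 standard-care patients in system 1 and 1334 − 600 = 734 in system 2.
- B, standard care at one third in both systems: 400 in system 1 and 934 in system 2.

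**Null contrast, HFNO v all standard care.** Pooled control risk p = (c1·r1 + c2·r2)/1334, where c1 and c2 are the control numbers. OR = [r2/(1−r2)]/[p/(1−p)]. Rejection ≈ Φ(|d|/s − 1.96) + Φ(−|d|/s − 1.96), with d = r2 − p and s its standard error.

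Scheme A with r1 = 15%, r2 = 20%: p = (600×15 + 734×20)/1334 = 17.75%; OR = 0.2500/0.2158 = 1.16; d/s = 0.0225/0.01515 = 1.49; rejection = 32%.

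| f = 0.3, risks (system 1 / system 2) | A: control risk, OR, rejection | B: control risk, OR, rejection |
|---|---|---|
| 15% / 20% | 17.75%, 1.16, 32% | 18.5%, 1.10, 17% |
| 15% / 10% | 12.25%, 0.80, 46% | 11.5%, 0.86, 24% |
| 15% / 17% | 16.1%, 1.07, 10% | 16.4%, 1.04, 7% |
| 15% / 16% | 15.55%, 1.03, 6% | 15.7%, 1.02, 6% |
| 15% / 15% | 15%, 1.00, 5% | 15%, 1.00, 5% |

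Under scheme A with the 5-point gaps, f = 0.1 gives 8–10% rejection and f = 0.5 gives 71–85%. Rates are for one fixed test and count both directions. For scale, the stated design OR is 0.625.

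**Restriction alone is not enough under steering.** In this set-up every standard-care patient could have received CPAP, so restricting the CPAP controls removes nobody. Under scheme B, CPAP has 800 patients from system 1 and 534 from system 2. With 15%/20%, the CPAP risk is (800×15 + 534×20)/1334 = 17.0% against 18.5% in controls: OR = 0.2048/0.2270 = 0.90 with no true effect. Stratifying by system returns 1.00.

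**Removing the steering alone is not enough either.** With fixed 1:1 and 1:1:1 and f = 0.3, system 2 has 2802/3 = 934 per arm. Pooled controls at 15%/20% have risk (600×15 + 934×20)/1534 = 18.04%, OR = 0.2500/0.2202 = 1.14, rejection about 22–23%.

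**Power in the valid HFNO comparison (15% v 10%, fixed test; unpooled / pooled variance).**
- f = 0.3, steered: A, 734 v 1334, 89.6% / 91.2%; B, 934 v 1334, 93.8% / 94.5%.
- f = 0.5, steered: A, 334 v 1334, 66% / 72%; B, 667 v 1334, 87.5% / 89.5%.
- Fixed ratios, no steering: f = 0.3, 934 v 934, about 90.5%; f = 0.5, 2001/3 = 667 v 667, about 79%.

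**The case against.** The strongest reply is that the protocol never states that all standard-care patients are controls for both devices. The statistical analysis plan is not shown and may define the comparison sets, and the covariates are given as examples, so availability is not ruled out. That stands against the stronger reading a reader might infer, namely that the pooled contrast is prescribed. It does not remove the point: the plain reading of sections 6.1 and 6.2.4 is the whole standard-care arm, the unadjusted model cannot absorb an availability effect, and the steering is an allocation rule fixed in section 2.9.1. An analysis plan would have to stratify to deal with it.

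Second, bias needs availability to be prognostic. The documents give no evidence of its size, and with equal risks the OR is 1.00 and the error rate 5%. This also stands. So a claim that the comparisons are confounded would go too far.

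Third, a reader might infer that holding 1:1:1 forces system 2 to under-allocate standard care. It does not: scheme B holds the ratio with standard care at one third throughout, and it roughly halves the excess rejection. Nor does the text support reading the choice of system as clinician preference, since it follows from a check of availability made beforehand.

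Fourth, minimisation on site may limit imbalance within sites. It cannot supply an arm where a device is absent, and site is not among the named covariates.

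**Conclusion.** The point holds in conditional form. As written, the protocol allows device availability to confound the primary and interim comparisons, and it answers only with a larger sample. At an assumed 30% CPAP-only share with 1:1:1 held, a 5-point risk gap moves the HFNO null OR to between 0.80 and 1.16, with single-test rejection of 17–46% depending on the gap's direction and the steering scheme. Gaps of 1–2 points give about 6–10%, and equal risks give 5%. Shares, gaps and scheme are all assumptions. What the documents do establish is the structure: allocation that varies with availability, no stated control set, and no availability factor in the minimisation or among the named covariates.

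Separately, exclusion 5 can be read as requiring both devices. On that reading system 1 would never be used and this concern would vanish, yet section 2.9.1 plainly provides for one-device randomisation. The two sections must be reconciled.

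**What to change.** 1. Sections 6.1 and 6.2.4: state that each device is compared only with standard-care participants randomised when that device was an option, and that the analysis is stratified by, or adjusted for, availability or randomisation system, at the interims as well as at the end. Both parts are needed for as long as allocation is steered.
2. Section 2.9.1: fix the ratio within each system (for example 1:1 in system 1 and 1:1:1 in system 2) and remove the steering across systems.
3. Count sample size and interim information per comparison in these sets.
4. Reconcile exclusion 5 with section 2.9.1.

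The cost is wording, a setting in the randomisation program, and some precision. Each comparison has fewer controls, and the standard-care arm becomes larger than each device arm. With the fixed ratios above, HFNO power for 15% v 10% is about 90% at a 30% CPAP-only share and about 79% at 50%, before any allowance for interims. This is why the information should be tracked per comparison. The allocation change is worth making early, because steering cannot be undone for patients already randomised; for them, stratification is the remedy.

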## **2.9.2 Post-randomisation withdrawals, exclusions and Moves out of Region**

Participants may be discontinued from the trial treatment and/or the trial at any time without prejudice. Unless a participant explicitly withdraws their consent, they should be followed-up wherever possible and data collected as per the protocol until the end of the trial.

## **2.10 Trial treatments / intervention**

Patients in all three treatment groups will be intubated and receive invasive mechanical ventilation if clinically required.

### **2.10.1 Continuous Positive Airway Pressure arm**

Continuous positive airway pressure will be administered according to local protocol/guidelines. Details of initial settings (CPAP Pressure and FiO2) will be recorded on the CRF. Administration of CPAP will not be protocolised and left to clinical discretion for management.

### **2.10.2 High Flow Nasal Oxygen**

High flow nasal oxygen will be administered according to local protocol/guidelines. Details of initial settings (Flow and FiO2) will be recorded on the CRF. Administration of HFNO will not be protocolised and left to clinical discretion for management.

### **2.10.3 Standard care**

Standard care will comprise regular ward level oxygen therapy according to local protocol/guidelines, and excludes escalation to CPAP and HFNO. Administration of regular oxygen therapy will not be protocolised and left to clinical discretion for management.

## **2.11 Blinding and contamination**

### **2.11.1 Methods for ensuring blinding**

This is an open-label study. However, while the study is in progress, access to tabular results by treatment allocation will not be available to the research team, patients, or members of the Trial Steering Committee (unless the Data Safety Committee advises otherwise).

In addition, the clinical staff delivering the interventions will not be blinded or masked, and therefore there is possibility that bias could be introduced by knowledge of treatment allocation through administration of interventions. Due to the exceptional circumstance of this study, it is not possible to protocolise the interventions or provide training for clinical staff to ensure that delivery of the treatment is standardised across the trial sites. We will assess this bias in the interim stages of the trial and present the trial data by each site and intervention to the Data Monitoring

Committee and Trial Steering Committee. Both our primary and secondary outcomes are objective and this will ensure that detection bias is reduced.

### 2.11.2 Contamination

It is likely that the intervention the patient is randomised to may not be the one that is allocated or the patient may have crossed over to one of the other interventions. In this case, we will still include the patient in the trial on an intention-to-treat basis. However, we will do additional statistical analyses which will accommodate for patients who did not conform to the allocated intervention by means of a compliers analysis (as detailed in the statistical analysis section).

### 2.12 End of trial

The study will end when 4002 participants have been randomised and the last participant has completed final follow-up. The study will be stopped prematurely if:

- Mandated by the Ethics Committee
- Following recommendations from the Data Monitoring Committee (DMC)
- Funding for the trial ceases

The Ethics Committee that originally gave a favourable opinion of the study will be notified in writing if the study has been concluded or terminated early.

## 3 METHODS AND ASSESSMENTS

### 3.1 Schedule of delivery of intervention and data collection

**Table 2.** Trial assessments

| Visit                                      | 1                 | 2                                                   | 3                                      | 4                                  |
|--------------------------------------------|-------------------|-----------------------------------------------------|----------------------------------------|------------------------------------|
| Visit Window
(No. Weeks $\pm$ No. Days) | Day 0
Baseline | Regular in-hospital
reviews
(at least weekly) | Day 30
( $\pm$ 2 days) † | Hospital
discharge † |
| Baseline data collection                   | ✓                 |                                                     |                                        |                                    |
| Randomisation                              | ✓                 |                                                     |                                        |                                    |
| Intervention                               | ✓*                | ✓*                                                  |                                        |                                    |
| Adverse events                             |                   | ✓                                                   | ✓                                      | ✓                                  |
| Survival status                            |                   | ✓                                                   | ✓                                      | ✓                                  |
| Outcome assessment                         |                   |                                                     | ✓                                      | ✓                                  |

\*- Intervention will be delivered up to point of death, tracheal intubation, or clinical determination that no ongoing need (palliation or improvement).

†- Participants to be followed-up to day 30 or hospital discharge, whichever comes later

